### 3.2. Eligibility Criteria and Data Collection

All women aged 30–40 years old undergoing IVF due to female/male factor or unexplained infertility will be considered eligible for the study. Advanced age has been identified as a negative factor for IVF success rates. The limit is around 40 years of age. After this age, a steep decline in pregnancy and delivery rates are observed [61,62]. As noted above, and based on the currently available evidence, GnRH agonist and GnRH antagonist COH protocols lead to comparable live birth rates [4]. For all these reasons, we chose to include women in the age range of 30 to 40. Two protocols of i. GnRH agonists and ii. GnRH antagonists for pituitary suppression, following stimulation with r-hFSH, will be administered to participants.

For the GnRH agonist protocol, Triptorelin [Gonapeptyl, 3.75 mg (Ferring Pharmaceutical Hellas A.Ε.) or Arvekap, 3.75 mg (Ipsen, EPE)] will be administered subcutaneously daily during the midluteal phase of the menstrual cycle.

For the GnRH antagonist protocol, ovarian stimulation will begin on the second day of the cycle, and the antagonist, either Cetrorelix (Merck Serono Europe Limited, Middlesex, UK) or Orgalutran (Merck Sharp & Dohme Limited, Hoddesdon, UK), will be initiated as soon as the leading follicle reaches a diameter of 14 mm. Once pituitary downregulation and ovarian suppression is achieved, ovarian stimulation with exogenous gonadotropins will start, while GnRH agonist administration will continue concomitantly until the day of hCG administration. Recombinant FSH in the form of either follitropin alpha (Gonal-F; Merck Serono Europe Ltd, London, UK) or follitropin beta (Puregon; Merck Sharp & Dohme Ltd., Hertfordshire, UK) will be administered subcutaneously.

Women outside the age span mentioned above or those undergoing natural or mild IVF protocols will be excluded from the study. The following patient data will be collected: age; BMI; type of infertility (i.e., male, female, or unexplained); relevant comorbidities associated with infertility (e.g., ovulatory disorders such as PCOS, tubal factors, or endometriosis); data from previous IVF cycles; levels of anti-Mullerian hormone (AMH); FSH; LH; prolactin; AFC; estradiol (E2) and serum progesterone in the early follicular phase; and data on the IVF cycle of the pathways’ measurements, such as the number and size of follicles at the time of triggering, and the number of aspirated follicles and oocytes retrieved. Successful or unwanted outcomes of the IVF cycle of the pathways’ measurements will also be recorded. Data will be collected within a secure online platform, further ensuring patient anonymity. Access to the platform will be granted strictly to members involved in the collection, analysis, or interpretation of data.

### 3.3. The Biological Samples

After the separation of the oocytes from the follicular fluid by the embryologists, the follicular fluid will be collected in a sterile test tube and transferred to the Laboratory of Biology of the Medical School of National and Kapodistrian University of Athens, Athens, Greece. The GC will be purified from the follicular fluid using the red blood cell lysing buffer (RLB) method, as described previously [63]. The measurement of the pathways’ activity will be performed on the isolated GC from the collected and retained follicular fluids using special ELISA kits (e.g., Phospho-mTOR (S2448) and Total mTOR ELISA Kit (ab279869), Human/Phospho-P70S6K (T421/S424) ELISA Pharma (SBRS1919), PathScan^®^ Phospho-YAP (Ser127) Sandwich ELISA Kit #48804, Human TAZ ELISA Kit) to measure phosphorylated forms of specific pathway proteins (mTOR, p70S6K-1 for mTOR-related activation and YAP-1 and TAZ for Hippo).

### 3.4. Intended Comparisons and Outcomes

The phosphorylated/unphosphorylated levels of the four downstream effectors of the investigated pathways within the isolated GCs will be compared between women receiving a GnRH agonist protocol and those being administered a GnRH antagonist protocol. Furthermore, a comparison of the activity of these two pathways will be made concerning certain desired or unwanted outcomes of the IVF cycle, during which the pathways’ measurements took place. Live birth after the cycle of measurements will serve as the primary outcome of the case-control study. Clinical pregnancy (defined as the presence of a gestational sac on ultrasound scan at 6–7 weeks of gestation), implantation rate (defined as the number of sacs detected divided by the number of embryo transfers), ongoing pregnancy (i.e., presence of a positive fetal heartbeat on ultrasound from a gestational age of 10 weeks onwards), miscarriage (i.e., loss of pregnancy before 22 completed weeks of gestational age), ectopic pregnancy, and OHSS will be the secondary outcomes of the study.

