## 1. Introduction

### 1.1. Controlled Ovarian Hyperstimulation (COH) Protocols

Controlled ovarian hyperstimulation (COH) is a determining stage for the success of in vitro fertilization (IVF) as it leads to the necessary pooling of oocytes available for retrieval and subsequent creation of embryos for intrauterine transfer [1]. COH may be divided into three distinguishable phases: firstly, stimulation of multi-follicular development (for which the following have been used: human menopausal gonadotrophin (hMG), a purified (p-FSH) or highly purified follicle stimulating hormone (hp-FSH), a urinary product with follicle-stimulating hormone (u-FSH) and luteinizing hormone (LH) activity, and various recombinant FSH (rFSH) and LH (rFSH/rLH)); secondly, pituitary suppression towards the prevention of the LH surge and premature ovulation through the administration of gonadotropin-releasing hormone (GnRH) agonists or antagonists; and finally, the triggering of oocyte maturation and ovulation by using human chorionic gonadotropin (hCG) or GnRH agonists [2].

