### 3.5. Data Analysis

Categorical variables will be presented as frequencies and percentages, whereas numerical variables will be presented as mean (standard deviation) or median (interquartile range) based on the normality of the data. A normality check will be performed by using the Shapiro–Wilk test. Independent samples *t*-test or Mann–Whitney U test (as per normality or not of data) will be utilized for comparisons regarding numerical variables, whereas chi-square or Fisher’s exact (if applicable) tests will be used for categorical variables. Following the pilot phase (during which the following analyses would be underpowered), further analyses are being planned. Comparisons of the pathways’ activity will be made by patients’ age (<35 vs. >35 years of age), by category of infertility (male, female, or unexplained), and by the female infertility-related factor (e.g., PCOS and endometriosis). Concerning the IVF outcomes, multivariable logistic regression models are further being planned.

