## 4. Conclusions

Based on data mostly derived from animal models or in vitro studies, it seems that controlled activation of mTOR, its related downstream effectors, and controlled inhibition of the Hippo pathway within the ovarian GCs may lead to a nurturing follicular microenvironment, reinforce the beneficial ovarian GC-oocyte interactions, and therefore positively influence oocyte quality and reproductive outcomes. Phosphorylated/unphosphorylated levels of the pathways’ main downstream mediators may be included among the intracellular biomarker candidates that feasibly provide a more “personalized” prediction of patients’ response to certain COH protocols and final IVF outcomes. Only at a very preliminary stage of this suggested effort, our study group proposes a prospective cohort study to compare the levels of certain phosphorylated/unphosphorylated components of the investigated pathways (mTOR, p70S6K-1, YAP-1, and TAZ) between GC isolated from the follicular fluid of women undergoing GnRH antagonist/“short” protocols and the ones from women receiving GnRH agonist/“long 21” protocols. After recording the desired/unwanted primary and secondary outcomes of the IVF cycle, a case-control design comparing these levels between women achieving the predefined endpoints and those who did not is further planned. Following the successful completion of the pilot phase, and given higher expected recruitment at later stages of the project, further analyses stratifying women by age groups and/or different etiological factors of infertility are planned to address the heterogeneity of the population. Notably, many studies in this direction are needed before any conclusions on the validity of the stated hypothesis can be drawn.

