## Figures and Tables

**Figure 1 jcm-11-06131-f001:**
[figure not shown]
Illustration of the prospective and case-control phases of the planned study. Eligible participants will be women aged 30–40 undergoing stimulated IVF cycle (i.e., not undergoing natural or mild IVF protocols) due to infertility of male, female factor, or unexplained etiology. The number of participants (100) refers to the targeted sample of the pilot phase. Following the successful completion of this phase, more study centers and subjects are intended to be included. (**a**) Prospective phase of the designed study. Levels of certain phosphorylated components of the investigated mTOR and Hippo pathways will be compared between women receiving GnRH agonist/“long 21”protocols and those receiving GnRH antagonist/”short” protocols. These levels will be measured via special ELISA kits by using follicular fluid-isolated ovarian GCs from each group. (**b**) Case-control phase of the planned study. Already measured levels of certain phosphorylated components of the investigated mTOR and Hippo pathways will be retrospectively compared between women achieving predefined (positive/negative) IVF endpoints and those not. Both schemes were created with Biorender.com (www.biorender.com, 19 September 2022). A license for the use of BioRender icons appearing in both schemes and the publication has been granted. Both schemes are original and were created by the authors. ***Abbreviations:*** GnRH, gonadotropin-releasing hormone; BMI, body mass index; AMH, anti-Mullerian hormone; FSH, follicle stimulating hormone; LH, luteinizing hormone; PRL, prolactin; AFC, antral follicle count; E2, estradiol; PG, progesterone; no, number; FF, follicular fluid; GC, granulosa cell; RLB, red blood cell lysing buffer; ELISA, enzyme-linked immunosorbent assay; mTOR, the mechanistic target of rapamycin; p70S6K-1, ribosomal protein S6 kinase beta-1; YAP-1, yes-associated protein-1; TAZ, transcriptional coactivator with PDZ-binding motif; OHSS, ovarian hyperstimulation syndrome.

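### Implantation rate is divided by transfer procedures rather than embryos transferred, so it varies with the number of embryos placed, and in the achieved/not-achieved comparison it duplicates clinical pregnancy

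*Protocol article*

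**What the plan says.** Section 3.4 makes live birth the primary outcome of the case-control part and names six secondary outcomes. One is "implantation rate (defined as the number of sacs detected divided by the number of embryo transfers"). The same sentence contains "Clinical pregnancy (defined as the presence of a gestational sac on ultrasound scan at 6–7 weeks of gestation"), which is a yes/no finding for each woman.

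Outcomes are to be related to the pathway measurements woman by woman. The Conclusions describe "a case-control design comparing these levels between women achieving the predefined endpoints and those who did not is further planned", and the Figure 1 legend says that the measured levels "will be retrospectively compared between women achieving predefined (positive/negative) IVF endpoints and those not". For the period after the pilot, section 3.5 adds: "Concerning the IVF outcomes, multivariable logistic regression models are further being planned".

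The introduction (section 1.1) refers to "subsequent creation of embryos for intrauterine transfer", in the plural. Nowhere does the article say that only one embryo is placed per transfer. The cycle data named in section 3.2 include "the number and size of follicles at the time of triggering, and the number of aspirated follicles and oocytes retrieved". The number of embryos transferred is not named, but the items are given only as examples.

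**The concern.** Numerator and denominator count different things. Each implanted embryo ordinarily gives one sac, whereas a transfer is a procedure that may place one embryo or several. The ratio therefore rises when more embryos are placed, even if no single embryo is more likely to implant.

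An implantation rate would be listed beside clinical pregnancy in order to describe what happens per embryo. Section 1.2 names implantation among the steps that depend on oocyte competence, so per-embryo information bears on the hypothesis. With procedures as the denominator that information is lost, and the reported figure cannot be read without knowing how many embryos were placed.

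There is also a question of fit. The outcome comparison sorts women into those who achieved an endpoint and those who did not, and the article does not say how a ratio is to be sorted. The obvious rule, any sac versus none, leads back to an endpoint already on the list.

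**Working it through.** The article reports no implantation rate and bases no calculation on one, so there is no figure to reproduce. The check is algebra on the stated definition. All values of *p* and *m* below are assumptions.

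**Inputs**
- Definition: sacs ÷ transfer procedures (section 3.4).
- Clinical pregnancy: at least one gestational sac (section 3.4).
- Unit of the outcome comparison: the woman, achieved or not (Conclusions; Figure 1 legend).
- *p*: probability that a transferred embryo gives a sac. Assumed, 0.20 to 0.60.
- *m*: embryos per transfer. Assumed, 1 to 3.

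**1. What the stated ratio estimates**

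Expected sacs per transfer = *m* × *p*. Expected sacs per embryo transferred = (*m* × *p*) ÷ *m* = *p*.

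| *p* | *m* = 1 | *m* = 2 | *m* = 3 | Per embryo |
|---|---|---|---|---|
| 0.20 | 20% | 40% | 60% | 20% |
| 0.30 | 30% | 60% | 90% | 30% |
| 0.40 | 40% | 80% | 120% | 40% |
| 0.50 | 50% | 100% | 150% | 50% |

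If a share *s* of transfers place two embryos and the rest one, the stated ratio is *p* × (1 + *s*). At *p* = 0.30:
- *s* = 0: 30%
- *s* = 0.25: 37.5%
- *s* = 0.50: 45%
- *s* = 0.75: 52.5%
- *s* = 1: 60%

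The per-embryo rate is 30% throughout.

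**2. Values above 100%**

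For one woman, two sacs ÷ one transfer = 2, or 200%. With two embryos implanting independently, the chance of this is *p*²: 4%, 9%, 16% and 25% at *p* = 0.2, 0.3, 0.4 and 0.5.

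The expected rate for a whole group exceeds 100% only when *m* × *p* > 1, for example 3 × 0.4 = 1.2 or 2 × 0.6 = 1.2.

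**3. The woman-level split**

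Take a woman with one transfer of two embryos:

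| Sacs | Sacs ÷ transfers | Sacs ÷ embryos | Any sac | Clinical pregnancy |
|---|---|---|---|---|
| 0 | 0 | 0 | no | no |
| 1 | 1 | 0.5 | yes | yes |
| 2 | 2 | 1 | yes | yes |

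With one transfer, the stated ratio is simply her sac count. It is above zero exactly when clinical pregnancy is present, assuming that the sacs are counted at the same scan. Changing the denominator does not alter this split, because a ratio is positive whenever its numerator is. For a woman without a transfer, both ratios are 0 ÷ 0 and undefined.

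**The case against.** The strongest reply is that the wording is probably a slip for embryos transferred, in one secondary outcome of a feasibility pilot, and that under single-embryo transfer the two denominators coincide. Both are fair and bear on severity. The printed definition is nevertheless the one that analysts would apply, and no other section corrects it or restricts transfers to one embryo.

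Several stronger readings are tempting, and the article does not support them.

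- **That the definition biases the comparison of agonist with antagonist protocols, or of age groups.** Section 3.4 compares marker levels between the protocols, and the age comparison in section 3.5 is also of pathway activity. No comparison of implantation rates between protocols or ages is stated.
- **That it distorts the achieved/not-achieved groups.** Under an any-sac split the groups are the same with either denominator. The weakness there is redundancy, not bias. The denominator matters when the rate is reported, or analysed as a number.
- **That the ratio measures transfer policy.** It is per-embryo implantation scaled by embryos per transfer, so it is confounded by transfer policy but still carries implantation.
- **That a ratio cannot define groups at all.** It can, at any sac versus none, but that is clinical pregnancy again.
- **That the number of embryos transferred will not be recorded.** The list in section 3.2 is open-ended, so this needs confirming and cannot be asserted.

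It can also be said that the choice of model belongs in an analysis plan that is not shown. That stands: a clustered binomial model is one option and its absence is not an error.

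**Conclusion.** The definition is wrong as printed and should be corrected. The severity is minor.

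As stated, the rate equals per-embryo implantation multiplied by embryos per transfer. Under the assumed 30% per embryo, it runs from 30% with only single transfers to 60% with only double transfers, and a woman with two sacs after one transfer scores 200%. The size in this study cannot be given, because the article reports neither the embryos per transfer nor an implantation probability. If every transfer placed one embryo, the effect would be nil.

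In the achieved/not-achieved comparison the outcome adds no information beyond clinical pregnancy. That conclusion assumes an any-sac split, the same scan for both outcomes, and women who had a transfer.

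Live birth, the other five secondary outcomes and the comparison of marker levels between protocols are unaffected.

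**What to change.** In section 3.4, define implantation rate as the number of gestational sacs divided by the number of embryos transferred. Confirm that the number of embryos transferred is on the data form, and add it if it is not.

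Then choose one use and state it:
- analyse the outcome as sacs out of embryos transferred, related to marker level, with allowance for several embryos coming from the same woman; or
- report the rate descriptively and leave it out of the achieved/not-achieved comparison, where clinical pregnancy already serves.

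The cost is one changed definition, one sentence on use and at most one routine data item. It is best settled before pilot data collection, so that the item is captured from the first participant and the corrected definition carries into the planned multicentre phase.

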### 3.5. Data Analysis

Categorical variables will be presented as frequencies and percentages, whereas numerical variables will be presented as mean (standard deviation) or median (interquartile range) based on the normality of the data. A normality check will be performed by using the Shapiro–Wilk test. Independent samples *t*-test or Mann–Whitney U test (as per normality or not of data) will be utilized for comparisons regarding numerical variables, whereas chi-square or Fisher’s exact (if applicable) tests will be used for categorical variables. Following the pilot phase (during which the following analyses would be underpowered), further analyses are being planned. Comparisons of the pathways’ activity will be made by patients’ age (<35 vs. >35 years of age), by category of infertility (male, female, or unexplained), and by the female infertility-related factor (e.g., PCOS and endometriosis). Concerning the IVF outcomes, multivariable logistic regression models are further being planned.

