## 3. Materials and Methods

### 3.1. Study Design

Comparison of the phosphorylated/unphosphorylated levels of the pathways’ components following the administration of GnRH antagonist/“short” protocols versus GnRH agonist/“long 21” protocols will be conducted through a prospective-cohort design. A comparison of levels between women achieving certain predefined outcomes within the IVF cycle and those not reaching these outcomes will be carried out through a case-control design. The pilot phase of the study, during which 100 women undergoing IVF are planned to be recruited, will be conducted in the Second Department of Obstetrics and Gynecology of “Aretaieion Hospital”, Athens, Greece, a tertiary academic center within a university IVF unit (Figure 1). Institutional review board approval will be received, and informed consent will be obtained from all participants. Following the potential success of the pilot phase, more public/private study centers are to be added towards the increased recruitment of the study subjects.

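### The agonist-versus-antagonist comparison of pathway levels is planned as an unadjusted two-sample test in a non-randomised cohort, although the main baseline covariates are collected

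*Protocol article*

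**What the plan says.** The first aim, in section 2, is framed as an effect: the choice of stimulation protocol may alter mTOR and Hippo activity in granulosa cells. Section 3.1 states that this comparison "will be conducted through a prospective-cohort design". Section 3.2 says that the two regimens "for pituitary suppression, following stimulation with r-hFSH, will be administered to participants" and gives no rule, random or otherwise, for who receives which. Section 3.4 states the contrast: levels of the four effectors "will be compared between women receiving a GnRH agonist protocol and those being administered a GnRH antagonist protocol".

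For the analysis, section 3.5 names an independent-samples t-test or a Mann–Whitney U "test (as per normality or not of data) will be utilized for comparisons regarding numerical variables". It places two further analyses after the pilot:

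- "Comparisons of the pathways’ activity will be made by patients’ age (<35 vs. >35 years of age), by category of infertility", and by female infertility factor. The Conclusions describe this as "further analyses stratifying women by age groups and/or different etiological factors of infertility are planned to address the heterogeneity of the population".
- "Concerning the IVF outcomes, multivariable logistic regression models are further being planned".

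Section 3.2 lists the baseline data to be collected. Besides age, BMI, infertility type, comorbidities such as PCOS and endometriosis, and previous IVF cycles, the list includes "levels of anti-Mullerian hormone (AMH); FSH; LH; prolactin; AFC".

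**The concern.** Without randomisation, the women on the two protocols may differ before stimulation starts. If a factor that differs between the groups is also related to a marker, a two-sample test attributes its influence to the protocol. The article gives reason to take this seriously. Eligibility is broad (ages 30–40, any female, male or unexplained infertility), and the Introduction links PCOS, endometriosis and ovarian ageing to altered activity in one or both pathways.

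At stake is the reading of the cohort's main result. A difference in phosphorylated mTOR or YAP-1 could be reported as a consequence of the protocol when it reflects who was given that protocol. More recruitment does not help: bias does not shrink with sample size while the standard error does, so a larger registry would make a spurious difference look more certain.

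**Working it through.** **No figure to reproduce.** The article gives a pilot target of 100 women, without alpha, power, effect size, SD or split by protocol. The check therefore has two parts: what the text assigns to the protocol contrast, and an illustration under stated assumptions.

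**Part 1: which analyses touch the protocol contrast**

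| Analysis in section 3.5 | Response | Compared by | Adjusts agonist vs antagonist? |
|---|---|---|---|
| t-test / Mann–Whitney | marker level | protocol | No covariates |
| Post-pilot comparisons | pathway activity | age, infertility category, female factor | Not stated |
| Post-pilot logistic models | IVF outcomes | not stated | No: marker level is not the response |

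The second row is the only possible route to adjustment. Nothing says that the protocols are compared within these strata or that stratum results are pooled into one estimate. The strata also leave out AMH, AFC, BMI and previous cycles.

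**Part 2: possible size**

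Assumptions, none from the article: no true protocol effect; one standardised baseline covariate differs by *m* SD between groups; its within-group correlation with the marker is *r*; marker SD is 1; equal groups of *n*; two-sided 5% test, normal approximation.

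- Bias: b = m × r
- Standard error: SE = √(2/n), which is 0.200 for n = 50 and 0.0894 for n = 250
- False-positive rate: 1 − Φ(1.96 − b/SE) + Φ(−1.96 − b/SE)

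Mildest case (m = 0.3, r = 0.2), n = 50: b = 0.06 and b/SE = 0.30, so the rate is 1 − Φ(1.66) + Φ(−2.26) = 0.060.

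Strongest case (m = 0.8, r = 0.5), n = 50: b = 0.40 and b/SE = 2.00, so the rate is 1 − Φ(−0.04) + Φ(−3.96) = 0.516.

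| m | r | Bias (SD) | Rate, 50/50 | Rate, 250/250 |
|---|---|---|---|---|
| 0.3 | 0.2 | 0.06 | 6.0% | 10.3% |
| 0.3 | 0.5 | 0.15 | 11.7% | 38.9% |
| 0.5 | 0.3 | 0.15 | 11.7% | 38.9% |
| 0.5 | 0.5 | 0.25 | 24.0% | 79.8% |
| 0.8 | 0.3 | 0.24 | 22.4% | 76.5% |
| 0.8 | 0.5 | 0.40 | 51.6% | 99.4% |

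For scale, the difference detectable with 80% power at 50/50 is (1.96 + 0.842) × 0.200 = 0.56 SD.

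**What stratification or adjustment would recover.** A simulation of 2,000 runs per sample size took m = 0.5, r = 0.5 and no true effect. The stratified analysis split the confounder itself in two, at the midpoint between the group means.

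| Analysis | Bias, 50/50 | Rate, 50/50 | Bias, 250/250 | Rate, 250/250 |
|---|---|---|---|---|
| Unadjusted | 0.247 | 23.5% | 0.249 | 79.6% |
| Two strata | 0.089 | 7.2% | 0.091 | 19.6% |
| Covariate in the model | −0.002 | 4.8% | 0.000 | 4.6% |

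Two strata on the right variable remove most of the bias but not all of it, and the remainder matters again at the larger size. Strata on a variable unrelated to the confounder would remove none of it.

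**The case against.** The strongest reply has four parts.

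**Stratification is planned.** A reader might infer that patient differences are ignored in every phase. The text does not support that. Section 3.5 and the Conclusions plan later comparisons by age and aetiology, including PCOS and endometriosis, expressly because the population is heterogeneous. If these were applied within protocol they would give partial control. This stands as a limit on the concern. What remains is that the link to the protocol contrast is unstated and that ovarian reserve, BMI and previous cycles are outside the strata.

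**Confounding is not shown.** A reader might also infer that protocol and patient type are in fact confounded. No assignment rule is given, so selection by clinician or patient is a supposition. The Introduction's remark on lower OHSS probability with antagonists describes a treatment effect, not a rule for choosing a protocol. Its remark that regimens act differently according to patient characteristics describes effect modification. The links of PCOS and endometriosis to the pathways say nothing about who receives which protocol. This stands too: what the article supports is a risk left uncontrolled.

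**It is a pilot.** Section 2 gives the pilot a feasibility purpose, and the Conclusions say many more studies are needed before the hypothesis can be judged. This lowers the urgency for the first 100 women. It does not remove the point, because no different analysis of the protocol contrast is named for the larger phase.

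**It is a condensed article.** Covariate lists and model forms are often left to an analysis plan. Here, however, the article names the test for numerical variables and assigns multivariable modelling to a different question. That is a stated choice, not an omitted detail. The comment in section 3.5 about low power in the pilot concerns the subgroup and logistic analyses, and does not rule out a linear model with a few covariates in 100 women.

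**Conclusion.** The concern holds in limited form. The protocol contrast is fixed as an unadjusted two-sample test in a non-randomised cohort. The later age and aetiology comparisons are not explicitly tied to it, the multivariable models address IVF outcomes, and AMH, AFC, BMI and previous cycles have no stated use in it. As planned, an observed difference could not be attributed to the protocol.

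Under the assumed ranges, bias is 0.06–0.40 SD, with a false-positive rate of about 6%–52% at 50/50 and 10%–99% at 250/250. The imbalance, the correlation, the equal split and the size of 250 per group are all assumptions. The 99% figure is the extreme corner and should not be read as a forecast; at the mild end the pilot's error rate is barely above nominal. The roughly 5% after adjustment holds only because the simulation has a single, measured confounder.

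This should be fixed for the pilot and must be in place before the larger phase starts.

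**What to change.** In section 3.5, make the main agonist-versus-antagonist comparison a prespecified covariate-adjusted analysis for each marker. One suitable form is a linear model on an appropriate scale, such as the log, reporting the adjusted difference or ratio with a 95% CI; a propensity-based analysis would also serve. Use pre-stimulation variables already collected: age, BMI, AMH or AFC, PCOS and endometriosis, and previous IVF cycles. Add centre once further centres join.

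Leave out variables that arise after exposure, namely follicle number and size and oocytes retrieved. Label the t-test and Mann–Whitney results descriptive. State whether the age and aetiology analyses compare protocols within strata, and describe how protocol is assigned in practice.

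The cost is a few degrees of freedom and some extra analysis. For example, protocol plus six covariate terms and an intercept use 8 of 100, leaving 92. No new patients or measurements are needed for the covariates listed. Adjustment does not remove confounding by unmeasured factors, and the plan should say so.
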